### Study population

Patients that meet the eligibility criteria (Table 1) will be recruited from each participating ICU over a 16-month period.

**Table 1 Tab1:** Inclusion and exclusion criteria

Inclusion criteria	Exclusion criteria
1. Age ≥ 18 years 2. Patient admitted to the ICU within the past 48 h 3. Personal consultee provides declaration of agreement for patient enrolment, retrospective patient consent 4. Non-invasive ventilation (CPAP) or invasive mechanical ventilation 5. At least two other organ failures as defined by scoring ≥ 1 points on two of the SOFA score domains 6. Likely to remain in the ICU for at least 4 days	1. Profound cardiovascular instability—infused vasopressors ≥ 0.5 μg/kg/min of norepinephrine; or in opinion of senior attending doctor 2. Profound coagulopathy (prothrombin time > 2.5 times normal, APTT > 2 times normal or platelet count ≤ 50), bleeding diathesis or on intravenous heparin infusion APTR ≥ 2 3. Neuromuscular condition—any previous or concurrent neurological condition or muscle disease 4. History of peripheral arterial vascular disease—any previous surgery or interventional procedure for peripheral arterial insufficiency; or any reason to clinically suspect arterial insufficiency of the leg, such as collateral history of claudication or examination findings of absent peripheral pulses 5. Prior amputation of a lower limb 6. Thigh circumference > 77 cm (technical limitations) 7. Unlikely to survive the ICU 8. Disseminated malignancy 9. Pregnancy 10. Previous, or current, deep vein thrombosis and/or pulmonary embolism 11. Positioned prone 12. Contraindication to pharmacological venous thromboembolism prophylaxis 13. Pre-existing significant cognitive impairment 14. Enrolled in a conflicting interventional trial 15. Lack of ability to communicate in verbal and written English 16. Patient hospitalised > 48 h prior to ICU admission 17. Frail skin, skin condition or soft tissue infection or other reason that prevents experimental use of upper limb

*APTR* activated partial thromboplastin time ratio, *APTT* activated partial thromboplastin time, *CPAP* continuous positive airway pressure, *ICU* intensive care unit, *SOFA* Sequential Organ Failure Assessment

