## Methods

### Primary objectives

The primary objective of the trial is to determine whether it is safe and tolerable to apply RVOS to a proximal lower limb of ICU patients.

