### Repetitive vascular occlusion stimulus (RVOS) intervention

Participants in the intervention arm will receive one session of RVOS treatment on day 1 and two sessions per day, at least 4 h apart, from day 2 to 10 of study enrolment or until ICU discharge if this occurs before day 10. For safety, the intervention leg will be examined daily before the first RVOS session for deep vein thrombosis (DVT) from the common femoral to popliteal vein using ultrasound (CX50 Philips Ultrasound with L12–3 linear array transducer). If DVT is suspected, RVOS or arterial assessment will not be performed and the clinical team will be notified immediately.

During the RVOS session, the participant will lie supine in a semi-recumbent position with the lower limbs extended. A pressure cuff (SC12LTM segmental pressure cuff; Hokanson, Bellvue, WA, USA) will be applied around the proximal right thigh with a bandage wrapped underneath to avoid skin irritation and bruising. Each RVOS session will last for 40 min and will include four cycles of 5 min cuff inflation to 50 mmHg above the average systolic blood pressure to completely occlude arterial flow distally to the limb [98], followed by 5 min of complete deflation (0 mmHg) (Fig. 3). Pressure in the pneumatic cuff will be controlled by an inflator and air source device (E20 Rapid Cuff Inflator and AG101 Cuff Inflator Air Source; Hokanson). Maximum cuff pressure will be 200 mmHg.

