#### Arterial vascular measures

Arterial vascular function will be assessed at the same time points as muscle evaluation, using techniques previously described [102]. The diameter and blood flow velocity of the right superficial femoral artery at rest and immediately following 5 min of ischaemia will be measured using B-mode and pulse Doppler ultrasound imaging, respectively. Ischaemia will be induced by application of a pneumatic cuff to the right thigh and inflation to 200 mmHg cuff pressure. Blinded investigators will analyse the diameter and blood flow velocity using the commercially available software Brachial Analyzer (Vascular Research Tools 5; Medical Imaging Applications, LLC, Coralville, IA, USA) to assess flow-mediated dilation (FMD) and reactive hyperaemic response, surrogate markers of vascular health. The reactive hyperaemic response is a transient increase in blood flow in response to ischaemic stimulus, and a marker of vasodilator capacity of resistance vessels. FMD assesses endothelial-dependent vasodilation of the conduit artery in response to increased blood flow and internal wall shear stress. The resting SFA diameter and blood velocity, reactive hyperaemic response and FMD will be compared between intervention and control participants at each time point.

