### Statistical analysis

The statistical analysis addresses the objectives of demonstrating the safety and tolerability of applying RVOS to the lower proximal limb of ICU patients, and assessing the feasibility of undertaking a larger-scale study to demonstrate efficacy. As a feasibility trial, the statistical analysis will primarily be exploratory in nature, and thus hypothesis generating rather than confirmatory.

The primary objective of safety will be evaluated based on the frequencies and percentages of adverse events categorised by severity, group and site. The tolerability will be evaluated by assessing VAS pain scores of the intervention arm at each time point in terms of means and standard deviations.

The main feasibility outcome of recruitment will be evaluated as the percentage of randomised participants out of total eligible patients. The number of participants randomised as a percentage of targeted recruitment will also be computed. If data are available, the average number of research assistants’ hours spent on recruiting one participant will also be computed. Retention will be evaluated as the proportion of participants remaining at each time point compared to the number recruited in each arm.

Descriptive statistics will be used to summarise all response variables by site, time point and treatment group. Means and standard deviations will be computed for continuous outcomes and frequencies and percentages will be computed for categorical/dichotomous outcomes. The relationship with potential confounding factors—such as site, demographic data, delirium during ICU stay, severity of illness, length of ICU stay, sepsis (defined using SOFA score), and use of drug treatment (such as corticosteroids, neuromuscular blocking drugs, statins and propofol)—will be explored.

The following inferential statistics will be performed strictly for the purpose of identifying the directions and magnitudes of effects rather than to evaluate the statistical significance of the results due to inadequacy of statistical power.

Outcome measures recorded at a time point (such as ‘timed up and go’ and ‘sit to stand’ assessment) and clinical outcomes (such as duration of mechanical ventilation and length of ICU and hospital stay) will be compared between the two arms using an independent-sample *t* test.

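### Exclusion criterion 17 names the upper limb, but every cuff in the trial goes on the thigh, and no other criterion covers leg skin or soft tissue

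*Protocol article*

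**What the plan says.** Table 1 (Study population) closes its exclusion list with item 17: "Frail skin, skin condition or soft tissue infection or other reason that prevents experimental use of upper limb".

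The rest of the article places the experimental procedures on the leg:

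- Primary objectives: to "determine whether it is safe and tolerable to apply RVOS to a proximal lower limb of ICU patients".
- RVOS intervention: the pressure cuff "will be applied around the proximal right thigh with a bandage wrapped underneath to avoid skin irritation and bruising".
- Arterial vascular measures: "Ischaemia will be induced by application of a pneumatic cuff to the right thigh and inflation to 200 mmHg cuff pressure". This test is done in both arms.
- Statistical analysis: the safety and tolerability aim is again described as "applying RVOS to the lower proximal limb of ICU patients".

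The other limb-specific exclusions also concern the leg. Item 4 covers arterial insufficiency, item 5 is "Prior amputation of a lower limb", and item 6 sets an upper limit on thigh circumference for technical reasons.

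**The concern.** An exclusion for fragile, diseased or infected skin is there to protect the site where the cuff is inflated. Here the site named in the criterion and the site that receives the cuff are different limbs. Followed literally, the rule could let in a patient whose thigh skin is damaged or infected and turn away a patient whose only problem is in the arm.

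Two things are at stake. Safety and tolerability of a lower-limb cuff is the primary objective, so the eligible population should be defined without ambiguity about that limb. Eligibility also sets denominators for feasibility results: Table 3 uses the percentage of potentially eligible patients who are missed, and the Statistical analysis section uses randomised patients as a percentage of all eligible patients. If the two sites read item 17 differently, they count eligible patients differently.

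**Working it through.** The article gives no figure to reproduce. The check sets the passages side by side and then works out the planned exposure.

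**1. Which limb gets a cuff?** Four places answer: Primary objectives (proximal lower limb), RVOS intervention (proximal right thigh), Arterial vascular measures (right thigh) and Statistical analysis (lower proximal limb). All four say the leg. No section places a cuff on the arm.

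**2. Is the arm used for anything else?** Yes. The Muscle strength section describes dominant-hand grip and manual testing of shoulder, elbow and wrist groups. These are outcome assessments without a cuff, done only when the patient is alert and free of delirium.

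**3. Does another criterion cover leg skin or soft tissue?** Items 4 to 6 are the other limb-specific exclusions. They address arteries, amputation and circumference. None mentions skin or soft tissue, and neither does any other item in Table 1 apart from item 17.

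**4. How can item 17 be read?**

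| Reading | Thigh skin disease or infection | Arm problem | Limb named matches cuff site? |
|---|---|---|---|
| The limb clause governs the whole list (natural reading) | Not excluded | Excluded | No |
| The limb clause governs only the catch-all reason | Excluded, as at any site | Skin problems excluded; other reasons excluded if they prevent use of the arm | No |
| The limb named is a slip for the upper part of the leg | Excluded | Not excluded | Only after correction |

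The consequence for patients depends on the reading. The mismatch in the printed wording does not.

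**5. Planned exposure of the thigh.** From the RVOS intervention section: one session on day 1, two per day on days 2 to 10, four inflations per session.

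- Sessions: 1 + 2 × 9 = 19
- Inflations: 19 × 4 = 76

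These are maxima for a patient who stays in the ICU to day 10. The arterial test adds a thigh inflation at baseline, day 6 and day 11 in both arms, so control patients are also concerned. These figures describe how much cuff use the criterion is meant to screen for. They do not say how many patients were misclassified.

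**The case against.** The strongest reply is that this is a slip of wording. Every passage on cuff placement agrees on the leg, so a screener would have little doubt which limb matters. The full protocol, case report form and screening log are not shown, so the error may exist only in the article. This stands as a limit on the consequence: the article cannot show that anyone was wrongly enrolled or excluded. It does not remove the contradiction, which nothing in the article resolves.

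A second reply is that safeguards exist. A bandage goes under the cuff, the leg is examined after each session, and a session stops on objective signs of tissue injury. These limit the possible harm, but they act after enrolment and do not replace an eligibility rule.

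A third is that an arm exclusion may have a purpose, since strength testing uses the arm. That is possible, so arm exclusions should not be called irrelevant. It would still not explain why the cuff site has no skin criterion of its own on the natural reading.

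A reader might also infer that the safety estimate is biased. The article does not support that. The named primary safety events are DVT, pulmonary embolism and creatine kinase above 3800 IU/L. Local skin injury is not among them and would count only if it met the general definition of a serious adverse event. Item 17 is applied before randomisation and to both arms alike, so at most it changes the population studied.

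**Conclusion.** The point holds as an internal contradiction in an operative eligibility criterion. Item 17 names a limb that receives no cuff, and no other criterion covers skin or soft tissue of the limb that does. That patients with thigh skin disease are admitted and patients with arm problems excluded follows only on the natural reading, in which the limb clause qualifies the whole item. On the narrower reading the skin items exclude at any site, and what remains is the mismatch of limb.

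The planned exposure is up to 19 sessions and 76 thigh inflations per intervention patient. The effect on patient numbers and on the screening figures cannot be derived from the article. No bias in the between-arm safety comparison is claimed.

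**What to change.** Reconcile item 17 with the limb that receives the cuff, and word it so that it is clear whether the limb clause applies to the skin items or only to the catch-all reason. If there is a genuine upper-limb reason, such as strength testing, list it as a separate item.

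The Trial status section says that recruitment was completed in February 2019, so a corrected criterion can no longer change who enters. What can still be done:

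- check item 17 against the full approved protocol, and correct the article if the error is only there;
- state in the results report how each site applied the item and which limb each skin exclusion concerned, as far as the screening log allows;
- carry only the corrected wording into the larger trial.

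The cost is a change of a few words and a look through the screening records. It does not touch the sample size or the analysis.

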### Recruitment and randomisation process

All sequential ICU admissions will be screened for eligibility. Eligible patients with mental capacity for informed consent will be approached, the risks and benefits of participation explained and written informed consent will be obtained before enrolment by the investigator physician. However, we envision that the majority of eligible patients will be receiving invasive mechanical ventilation and requiring sedation, and thus lacking capacity to consent. In this instance, declaration of agreement will be sought from the patient’s ‘Personal Consultee’ who may be a representative, partner or close friend. Once the participant recovers and is capable of understanding the details of the trial, they will be approached to provide their informed consent retrospectively. If the patient chooses to withdraw from the trial, they will be given the choice of having their existing data and samples destroyed or excluded from final analysis.

Upon informed consent or declaration of agreement, eligible patients will be randomised to either the intervention arm or the control arm in a 1:1 ratio. Separate randomisation lists have been prepared for each site by an independent statistician and uploaded to the study electronic data capture system PROMASYS (Surrey Clinical Trials Unit). In addition, the randomisation list and corresponding envelopes containing randomisation assignments will be stored in the trial file. Randomisation, outcome measure assessments and RVOS intervention will be performed by a research assistant unblinded to patient allocation.

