**Fig. 3 Fig3:**
[figure not shown]
Protocol for repetitive vascular occlusive stimulus (RVOS). Each session of RVOS includes four repetitions of 5-min inflation of pneumatic cuff to 50 mmHg supra-systolic blood pressure (SBP) followed by 5 min of complete (0 mmHg) cuff deflation

Vital signs such as blood pressure, heart rate and the saturation of peripheral arterial blood with oxygen will be monitored before and during RVOS, and the session will be terminated if the defined criteria are met (Table 2).

**Table 2 Tab2:** Termination criteria for repetitive vascular occlusion stimulus (RVOS) session

1. Heart rate < 40 bpm or > 180 bpm 2. Systolic blood pressure < 80 mmHg or > 200 mmHg 3. Mean arterial blood pressure < 60 mmHg or > 120 mmHg 4. Peripheral capillary oxygen saturation (SpO_2_) < 88% 5. Pain score > 8/10 on visual analogue scale and unwillingness to proceed with RVOS intervention 6. Objective signs of tissue injury felt due to cuff inflation	

A clinical bedside nurse will be present throughout the RVOS session and will monitor facial expression, limb movement and ventilation compliance for any sign of distress in the sedated participants. In the event that the patient experiences significant discomfort, the cuff pressure will be lowered to a pressure that is tolerated by the participant, and such adjustments will be recorded. If conscious, tolerability of the intervention will be evaluated by asking the participant to rate the pain of the procedure on a visual analogue scale (VAS). After each session, the intervention leg will be examined for signs of arterial insufficiency or tissue injury. In addition, serum creatinine kinase levels will be monitored daily as an indicator of muscle damage.

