### Primary outcome measures

#### Safety

The number of serious adverse events (SAEs; DVT, pulmonary embolism and elevated serum creatine kinase concentration (creatine kinase > 3800 IU/L)) will be compared between the control and intervention groups.

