#### Tolerability

The VAS pain score will be used to assess the tolerability of RVOS.

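### The withdrawal rule names only destruction or exclusion of existing data, so withdrawals related to pain or harm can selectively remove primary tolerability and safety data

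*Protocol article*

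**What the plan says.** The Recruitment and randomisation process section of the Protocol article expects most eligible patients to be sedated and to enter on a personal consultee's agreement. After recovery, "they will be approached to provide their informed consent retrospectively". If a patient then decides to withdraw, "they will be given the choice of having their existing data and samples destroyed or excluded from final analysis". The sentence is not limited to retrospective consent, so it also covers patients who consented for themselves before enrolment.

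The primary objective is to "determine whether it is safe and tolerable to apply RVOS to a proximal lower limb of ICU patients". For safety, the numbers of SAEs (DVT, pulmonary embolism, raised creatine kinase) "will be compared between the control and intervention groups". For tolerability, "The VAS pain score will be used to assess the tolerability of RVOS", and the Statistical analysis section specifies "assessing VAS pain scores of the intervention arm at each time point in terms of means and standard deviations".

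**The concern.** The choice is between two outcomes, and each removes the patient's data from the analysis. Whether a patient's data count therefore depends on a decision made after randomisation, and often after RVOS has been given and the pain score recorded. If that decision is related to pain or harm, the missing data are informative for the very outcomes the trial exists to measure.

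At stake is the reading of the primary results. Tolerability is a mean in one small arm, so a few high scores matter. The Discussion makes a later powered trial depend on RVOS proving safe, feasible and acceptable, so a flattering tolerability figure would carry forward into that decision.

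**Working it through.** The plan gives no withdrawal rate and no figure on this point, so there is nothing of its own to reproduce. The check sets the rules side by side and then illustrates the effect under stated assumptions.

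**Who can supply VAS data, and who can have it removed.** The RVOS intervention section asks for a VAS score only from conscious patients, and the Discussion says tolerability cannot be assessed under ventilation and sedation. Patients who can score pain are thus largely those who have, or later regain, the capacity to withdraw. The two groups overlap by design.

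**Exposure by arm.** RVOS is one session on day 1 and two per day on days 2 to 10, each with four inflations:
- sessions: 1 + 2 × 9 = 19 at most
- inflations: 19 × 4 = 76 at most

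Controls are not wholly free of the cuff. The Arterial vascular measures section uses one thigh-cuff occlusion per assessment in both arms, at baseline, day 6 and day 11, so three at most. Withdrawal because of repeated RVOS can arise only in the intervention arm.

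**Illustration for VAS.** Inputs:
- 16 patients with a VAS score: the planned ICU survivors per group (Sample size rationale), assuming that all of them score
- mean with everyone kept, 3.6: quoted in the Background from patients with subarachnoid haemorrhage
- k withdrawers, each scoring 9: assumed

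Mean after exclusion = (16 × 3.6 − 9k) / (16 − k)
- k = 1: (57.6 − 9) / 15 = 3.24
- k = 2: (57.6 − 18) / 14 = 2.83
- k = 3: (57.6 − 27) / 13 = 2.35

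The other way round, suppose the patients who stay average 3.6. The mean with everyone kept is then (9k + 3.6 × (16 − k)) / 16:
- k = 1: 63.0 / 16 = 3.94
- k = 2: 68.4 / 16 = 4.28
- k = 3: 73.8 / 16 = 4.61

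The reported figure would be 3.60 in each case, so the understatement is 0.34, 0.68 or 1.01 points. Both versions point the same way. If only 8 patients were awake to score (an assumption), one exclusion would give (8 × 3.6 − 9) / 7 = 2.83, so each loss weighs more.

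**Share of the safety denominator.** SAEs are counted in all randomised patients, not only ICU survivors. With 32 survivors needed and 30% deaths expected, 32 / 0.7 = 45.7 patients, or about 23 per arm. The planned yield of 47 gives 23.5 per arm. One exclusion is therefore about 1 / 23.5 = 4.3% of an arm.

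**The case against.** The strongest reply is that intolerance is not withdrawal. For significant discomfort the protocol has the cuff pressure lowered and the change recorded. The Table 2 criterion "Pain score > 8/10 on visual analogue scale and unwillingness to proceed with RVOS intervention" ends the session, not participation. A patient who finds RVOS intolerable can stay in the trial with scores and adjustments on file. This stands. A reader might infer that the rule removes the patients who could not tolerate RVOS, but the documents do not support that. It reaches only those who leave the trial, and no section links withdrawal to pain. What remains is that if such a patient does later withdraw, those recorded scores and adjustments are what leave the analysis.

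A second reply is that the sentence may describe a right to removal, with retention otherwise, and that the consent form is not shown. That reading is possible, but the text names two outcomes and does not state it. If it was meant, the wording needs correcting.

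A third concerns safety. SAE forms reach the sponsor within 24 h, and the independent Trial Safety Group is updated after every five patients or any SAE, so events are not hidden from oversight. That stands too, but it does not restore an excluded event to the final comparison. Nothing shows that patients with DVT, pulmonary embolism or raised creatine kinase withdraw more often, so a reader should not conclude that RVOS will look safer.

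Finally, retention is already measured against the number recruited in each arm, so differential loss would show. It would not show the scores or events of those who left. Controls may withdraw as well, so imbalance between arms is a risk and not a certainty.

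**Conclusion.** The point holds as a defect in a stated rule, not as a prediction of bias. Taken as written, the rule permits outcome-related exclusion after randomisation from the primary tolerability and safety results. The route is clearest for VAS, which is summarised in the intervention arm alone. For SAEs it is a possibility without evidence of direction.

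The size is unknown. The falls from 3.6 to 3.2, 2.8 or 2.4 rest on an assumed number of withdrawals, an assumed score of 9, a mean from another population and all 16 survivors giving a score.

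Two further inferences should be avoided. One is that only survivors who regain capacity can be lost this way; patients who consented with capacity at enrolment can withdraw too. The other is that each exclusion costs 6.25% (1/16) of the safety denominator; that counts ICU survivors only, whereas about 4% of the expected randomised arm is the right order.

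**What to change.** Add a third choice beside the two already offered: the patient ends trial procedures but agrees that data collected up to withdrawal are kept. Include those data in the safety and tolerability analyses. Keep destruction and exclusion as choices that are actively offered. Restricting them to patients who ask would weaken a protection for people enrolled without their own consent, and the point does not need it.

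Report the number of withdrawals and the number of data exclusions by arm, with timing and any reason given. The analysis plan can carry this, since it is to be finalised before database lock.

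The cost is an amendment to the consent wording. Some loss will remain where patients choose removal, and choices already made must stand. The Trial status section says recruitment was completed in February 2019, so the wording change mainly serves patients still to be approached and the follow-on trial. The reporting can still be added to this trial if the database is not yet locked.
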